### Exclusion criteria

Contraindications for surgical therapy, according to the medical guideline, e.g. Inadequate liver, bone marrow, and kidney function or coronary heart disease (NYHA III-IV).Lacking ability to understand, speak and write GermanBeing admitted to a nursing home permanently.

### Primary endpoint

The effectiveness of SCAN program will be assessed on an individual patient level by comparing the proportion of patients who achieved a clinical relevant improvement of their HRQoL by 10 pts. At 8 weeks after discharge from hospital.

### Secondary endpoints

An overview on primary and secondary endpoints and the study timeline is provided in Table 1:

**Table 1 Tab1:** Outcome measures and measure times

Measure times		T0	T1	T2
Outcomes & Instruments		Baseline (day before discharge)	Primary measurement (8 weeks after discharge)	Follow-up (8 months after discharge)
HRQoL (primary outcome)	EORTC QLQ-C30 + EORTC-QLQ CR29	x	x	x
Utilization of adjuvant chemotherapy			x (if appropriate)	x
Supportive Care Needs and individual resources	FU-T 37		x	x
Distress	Distress Thermometer (DT)		x	x
Symptoms and functional impairments	MD Anderson Symptom Inventory		x	x

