### Intervention

Feasible patients are assessed by the participating study centers and registered to the coordinating trial center. Patients meeting the inclusion criteria and signing a written informed consent are randomized into the study arms. Patients in the intervention group are offered an additional nursing intervention after discharge for 8 weeks. The intervention time-line was adjusted to the actual S3-guideline on the treatment of colorectal cancer regarding the recommended latest onset of adjuvant chemotherapy. The intervention consists of a standardized protocol-based telephone follow-up serving once per week to disclose patients’ current supportive needs and in order to detect therapy-related physical and psychological impairments as early as possible. Standardized protocols were developed beforehand to ensure both consistent assessment and patient information during the counseling. Additionally, the SCAN is at patients’ disposal for contact from the beginning of primary therapy during the inpatient stage to outpatient aftercare for up to eight months. The intervention covers the entire period of transition from acute clinical care to out-patient aftercare.

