### In-patient period

Patients in the intervention group are visited twice by a specially trained oncology nurse (Supportive Cancer Care Networker, SCAN) during their inpatient stay. Both visits take about 30 to 60 min. Fist, patients are given relevant information, i.e. contact with specialists, voluntary services and the next steps and appointments of the treatment plan on the second last day before discharge from hospital. Second, at the last day before discharge the SCAN takes up the contact information and appoints weekly telephone consultations for eight weeks. Patients are handed out written information materials and the study documents, as for example, patient-held records (PHR), are explained. The PHR is derived from a newly generated 37-item generic supportive needs questionnaire “*Fragebogen zur Erfassung von Unterstützungsbedarfen von Tumorpatienten*“(FU-T). To ensure that patients are enabled to inform structured and completely about relevant changes of their medical condition, filling in the PHR is practiced under instructions. In coordination with the treating clinicians, critical events in which an immediate contact to the SCAN should occur are listed individually.

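### As written, the baseline for the primary 10-point improvement comes after allocation and after the intervention arm's first in-patient visit, so it can already be shifted in one arm only

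*Protocol article*

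**What the plan says.** All references are to the protocol article.

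- **Endpoint (Primary endpoint).** Effectiveness is judged by "comparing the proportion of patients who achieved a clinical relevant improvement of their HRQoL by 10 pts", assessed 8 weeks after discharge.
- **Baseline (Secondary endpoints, Table 1).** The QLQ-C30 and CR29 are given at T0, T1 and T2, and T0 is headed "Baseline (day before discharge"). T0 is the only quality-of-life measurement before the 8-week one.
- **Randomisation (Intervention).** "Patients meeting the inclusion criteria and signing a written informed consent are randomized into the study arms". No T0 questionnaire is named as a step before this.
- **In-patient visits (In-patient period).** "Patients in the intervention group are visited twice by a specially trained oncology nurse", for 30 to 60 minutes each time. The first visit covers specialist contacts, voluntary services and "the next steps and appointments of the treatment plan on the second last day before discharge from hospital". For the second: "Second, at the last day before discharge the SCAN takes up the contact information". At that visit the patient also receives written materials and has the patient-held record explained.
- **Content (Out-patient period).** The informed-decision component of the intervention is said to begin at the in-patient consultations.
- **Awareness (Blinding; Auditing).** Patients are stated to be blinded. Auditing adds that they are not told their group but might be aware of it, and that the nurses who deliver the intervention and assess outcomes do know it.

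**The concern.** A change score compares the arms cleanly when its starting value is recorded before allocation can affect it. Here the starting value is recorded, in one arm only, after a visit that belongs to the programme. If that visit reassures patients and raises T0, fewer of them can gain a further 10 points, and part of a real benefit is subtracted from itself. If the visit, or a sense of which group one is in, lowers T0, more patients reach 10 points without being any better at 8 weeks.

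Intention-to-treat analysis does not correct this, nor do the covariates listed under Primary endpoint analysis. Adding T0 as a covariate would not correct it either, because T0 would itself be a post-randomisation measurement. An untreated T0 cannot be recovered once the questionnaire has been completed late.

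**Working it through.** **1. Order of events as written, intervention arm**

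| Time | Event | Section |
|---|---|---|
| After surgery | Eligibility, consent, randomisation | Study population; Intervention |
| Second last day before discharge | Visit 1, 30–60 min | In-patient period |
| Last day before discharge | Visit 2, 30–60 min | In-patient period |
| Day before discharge | T0 QLQ-C30/CR29 | Table 1 |
| After discharge | Weekly calls for 8 weeks | Intervention |

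No sentence dates randomisation against T0. The order follows because visit 1 goes only to patients already in the intervention group and falls one day before T0. Visit 2 and T0 share a day, with no stated sequence. The control arm has no such visits.

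**2. The plan's own figure**

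Inputs from Sample size: 48% against 63% responders, 80% power. Two-sided 5% is assumed, since no alpha is stated.

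- Mean proportion p̄ = (0.48 + 0.63)/2 = 0.555; difference d = 0.15.
- n = [1.960·√(2·0.555·0.445) + 0.842·√(0.48·0.52 + 0.63·0.37)]² / 0.15² = 171.1, so 172 per arm.
- With continuity correction: (n/4)·[1 + √(1 + 4/(n·d))]² = 184.2, so 185 per arm.

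This matches the stated 185 per arm (370 in total). The sample size is not in question. It assumes that the 15-point difference is measured from an undisturbed baseline.

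**3. What a one-arm shift in T0 would do (illustration)**

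Assumptions not in the documents: the change score is normal, its SD is 20 to 30 points, and T0 is shifted by 2 or 4 points in one arm with the 8-week score unchanged.

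If a proportion p improves by at least 10 points, the mean change is 10 + SD·z(p). Raising T0 by s lowers every change by s, so the new proportion is Φ(z(p) − s/SD). With p = 0.48, z(p) = −0.050.

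| Rise in T0 | SD 20 | SD 25 | SD 30 |
|---|---|---|---|
| 0 points | 0 | 0 | 0 |
| 2 points | −3.97 | −3.18 | −2.65 |
| 4 points | −7.88 | −6.32 | −5.28 |

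Entries are changes in the responder rate in percentage points. Example: 2 points with SD 20 gives Φ(−0.050 − 0.100) = 44.03%, and 44.03 − 48 = −3.97. Against the planned 15 points the range is 2.65/15 = 18% to 7.88/15 = 53%. A fall in T0 has nearly the same size with the opposite sign (+2.66 to +3.99 for 2 points, +5.31 to +7.96 for 4 points).

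**4. Same calculation from the planned 63%**

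With z(0.63) = 0.332, a rise of 2 points lowers the rate by 2.5 to 3.8 points, and a rise of 4 points by 5.1 to 7.8. With 185 per arm, two-sided 5% and no continuity correction, power is 83% with no shift, 58% to 67% with a 2-point rise and 29% to 48% with a 4-point rise.

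**The case against.** The case for leaving the plan alone has several parts.

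- **The first visit is short and mostly informational.** Symptom monitoring and telephone support come after discharge, and nothing in the protocol shows that one such visit moves global health status. This stands as a limit on size. It does not make T0 a pre-intervention measurement, since the protocol itself starts the informed-decision content in hospital.
- **A reader might infer that T0 is answered by patients who know their group.** The documents do not support that as fact. They say patients are blinded and, elsewhere, that they might be aware; only the nurses are stated to know. The point does not depend on patient awareness, because visit 1 alone precedes T0.
- **A reader might infer that the primary result will be biased in the intervention's favour.** Neither bias nor its direction is established. A helpful visit would raise T0 and make the result conservative; inflation needs T0 to fall. If the programme moves neither T0 nor the 8-week score, the comparison remains valid.
- **The 2- and 4-point shifts have no source in the documents.** Correct. They show sensitivity and do not estimate a bias.
- **Figures 1 and 2 are not available and might show another order.** Also correct. If they do, Table 1 and In-patient period still need to be reconciled with them.
- **The 8-week score can be compared without T0.** True, and this limits the damage, but it answers a different question from the stated primary endpoint.

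**Conclusion.** The concern holds as a weakness in the timing of the primary baseline. On the text available, T0 follows allocation and the first in-patient visit in one arm, and falls on the day of the second. The protocol therefore permits a one-arm shift in the value from which the 10-point improvement is counted. The size and direction of any shift are unknown, and it may be nil. Under the assumptions shown, each 2 points of shift is worth roughly 2.7 to 4.0 percentage points of responder rate, which is not negligible beside a planned difference of 15. The documents do not show that such a shift occurs, that patients know their allocation at T0, or that the trial's result would be invalid. The change is worth making because it removes a possible bias in the primary endpoint at little cost.

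**What to change.** State one order and enforce it: written consent, then T0 QLQ-C30/CR29, then fax randomisation, then the first in-patient visit. Have the centre confirm T0 completion on the randomisation fax, so that no allocation is released without it. Align Table 1, Intervention and In-patient period with that order, and check Figures 1 and 2 against it.

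For patients whose T0 came after visit 1, record that fact and add a sensitivity analysis comparing the 8-week score itself between the randomised arms, without using T0. Randomisation protects that comparison, although it concerns level and not improvement.

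The costs are one confirmation item on the fax form and an earlier questionnaire. T0 moves a day or more closer to surgery, which may slightly change the response rate in both arms relative to the assumed 48%. The schedule also becomes tighter for patients identified late, since eligibility depends on post-operative histology. The sample size inputs and the intervention content need not change.

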### Sample size

For sample size calculation the portion of the patients who reach a clinically relevant improvement of the global health-related quality of life (HRQoL) within 8 weeks after discharge from hospital is chosen. The sample size calculation is based on an expected response difference of 15% points in the subscale *“global health status”*/QoL of QLQ-C30 EORTC between the intervention and the standard treatment 8 weeks after the clinic dismissal after surgical therapy. Own reference data [30] show a response of 48 % in standard treatment, so that in the intervention group responses of 63 % are expected. To be able to detect a relevant effect of the intervention with a rise of the responses by 15% points with 80 % power, *n* = 370 patients (*n* = 185 patients per study arm) are needed. Including a dropout rate of approx. 10 %, *n* = 406 patients (*n* = 203 per study arm) will be recruited.

### Randomization

Randomization on an individual level, patient enrollment and group allocation will be performed by fax from the Institute of Medical Epidemiology, Biostatistics, and Informatics (IMEBI), Halle as an external and independent unit. Randomization will be stratified by center using blocks of variable length from a reproducible SAS PROC PLAN code. A consecutive analysis of non-responders and of the causes for changes in therapy regimes is intended additionally due to the high therapy-related impairments in wellbeing and quality of life during adjuvant chemotherapy.

### Blinding

Patients are blinded for this study. A distinct patient number is allocated in case of inclusion in the study. A blinding of the medical staff (physicians, oncology nurses) is impossible due to the frequent re-admission of patients to be expected and the disclosure of information in the patient-held records.

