
### Follow-up

In order to determine differences in healthcare services utilization between intervention group and controls, all patients are asked to fill out additional written questionnaires at 8 weeks and 8 months after discharge from hospital. At both times, patient’s adherence to medical recommendations and completion of medical therapies is assessed as well.

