### Auditing

To realize quality assurance the Institute for Health and Nursing Science as the coordinating center of the study will provide an advanced support for documentation and study management in the recruiting centers. Trained research staff will visit each center at least 4 times. Pre-study-visit (1): the practice team will be introduced into the trial procedures, qualification of practice staff and research capacities building and documentation will be checked. Study visit (2 & 3): support for follow-up and data management with special attention on reporting AEs and SAEs. Post-study-visit (4): final query management. Additional audits can occur at any time during or after completion of the study. Monitoring will be performed regularly by verifying key data (signed informed consent form, inclusion and exclusion criteria and key baseline data). The research staff will be trained in source data verification and will be supported in preparing standardized reports.

To ensure the implementation of the intervention, quality audits are being conducted in the intervention groups in all study centers based on the guidelines of the Royal Collage of Nursing [40] and the German Network of Quality Assurance in Nursing Care [41]. The audit is based on (1) regular monitoring of the trained nurses’ knowledge about the training module, and (2) on an additional comparison of nursing records with study documentation for 10 % of all included patients. Nurses who administer the interventions and assess the outcomes are aware of group allocation due to their participation in the training to manage the SCAN intervention. Patients are not informed about group assignment, but might be aware of it due to unmasking information from nurses. Group allocation perception of included patients will be assessed at follow-up.

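### The Blinding section calls patients blinded, but they can see the intervention and the Auditing section contradicts it; the self-reported primary endpoint is therefore open to reporting bias

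*Protocol article*

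**What the plan says.** The Blinding section makes two statements. For patients: "Patients are blinded for this study". For staff: "A blinding of the medical staff (physicians, oncology nurses) is impossible".

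The Auditing section returns to the subject in different terms. On staff: "Nurses who administer the interventions and assess the outcomes are aware of group allocation". On patients: "Patients are not informed about group assignment, but might be aware of it due to unmasking information from nurses". It then adds a check: "Group allocation perception of included patients will be assessed at follow-up".

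The intervention is set out under In-patient period and Out-patient period. "Patients in the intervention group are visited twice by a specially trained oncology nurse", for 30 to 60 minutes each time. At the second visit the nurse explains the patient-held record and "appoints weekly telephone consultations for eight weeks". The Objectives name usual care as the comparator, and no attention control is described. The Study population section requires fully informed written consent before any data collection or counselling.

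The primary endpoint is the proportion of patients whose HRQoL improves by 10 points at 8 weeks; the Sample size section identifies the scale as QLQ-C30 global health status/QoL. On collection, the Follow-up section says "all patients are asked to fill out additional written questionnaires at 8 weeks and 8 months after discharge from hospital".

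**The concern.** The article gives the trial a property that its own description rules out. A patient who has agreed to a study of extra nurse support, and is then visited twice and telephoned every week, knows which group that is. A patient who gets no visits or calls can work out the other.

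This matters because the primary endpoint is the patient's own rating, cut at a 10-point change. If people who know they received support rate themselves somewhat higher for that reason alone, the responder proportion rises in one arm only. Randomisation, the intention-to-treat analysis and the covariate adjustment listed under Primary endpoint analysis do not remove such a difference.

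The Auditing section adds a second possible route, because it gives an assessment role to the nurses who deliver the intervention. A reader who relies on the Blinding section alone would conclude that patient awareness had been dealt with by design.

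**Working it through.** **1. The statements side by side**

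| Question | Blinding section | Elsewhere in the article |
|---|---|---|
| Do patients know their group? | Blinded, no qualification | Auditing: not told, but may be aware |
| Can they tell from what they receive? | Not addressed | In-patient and Out-patient periods: two visits, patient-held record, weekly calls; Objectives: usual care as comparator |
| Is staff blinded? | No | Auditing: no, and these nurses also assess outcomes |
| Who completes the follow-up forms? | Not addressed | Follow-up: patients, in writing |

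The first row is a contradiction. The second shows which side of it is tenable: receiving the intervention unmasks the patient, with no disclosure by a nurse needed. The Auditing section attributes unmasking only to information from nurses, so it too understates the problem.

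**2. The plan's own figure**

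Inputs from Sample size: 48% against 63%, 80% power, equal arms. The significance level is not stated there; two-sided 5% is assumed, in line with the 95% confidence interval under Primary endpoint analysis.

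- Without continuity correction: n = [1.960·√(2·0.555·0.445) + 0.842·√(0.48·0.52 + 0.63·0.37)]² / 0.15² = 171.1, so 172 per arm.
- With continuity correction: (171.1/4)·[1 + √(1 + 4/(171.1·0.15))]² = 184.2, so 185 per arm and 370 in total, as stated.

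The sample size reproduces and does not depend on this point.

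**3. How far reporting bias could move the test (illustration only)**

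The document gives neither the size of any bias nor the SD of the change score. Both are assumed: a lift of s = 2 to 5 points in the reported 8-week score in the intervention arm, change SD = 20 to 30, normally distributed change, and no true effect. Control response is 48% with 185 per arm.

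- Apparent intervention response: p₂ = Φ(Φ⁻¹(0.48) + s/SD), with Φ⁻¹(0.48) = −0.050.
- With d = p₂ − 0.48, se₀ the pooled and se₁ the unpooled standard error, two-sided rejection = Φ((d − 1.96·se₀)/se₁) + Φ((−d − 1.96·se₀)/se₁).

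Worked for s = 5, SD = 20: p₂ = Φ(−0.050 + 0.250) = 57.9%; d = 0.099; se₀ = 0.0519; se₁ = 0.0516; first term Φ((0.0992 − 0.1017)/0.0516) = 0.48; second term negligible.

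| Lift s | SD | Apparent response | Rejection favouring intervention (nominal 2.5%) | Two-sided rejection (nominal 5%) |
|---|---|---|---|---|
| 2 | 30 | 50.7% | 7.4% | 8.0% |
| 2 | 20 | 52.0% | 11.6% | 11.9% |
| 5 | 30 | 54.6% | 24.7% | 24.7% |
| 5 | 20 | 57.9% | 48.1% | 48.1% |

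The two rejection columns have different nominal levels and should not be mixed.

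**4. A second parametrisation**

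If bias adds 2, 3, 5 or 10 percentage points directly to a 48% response, rejection in favour of the intervention is 5.8%, 8.3%, 15.9% or 48.7% against 2.5%, and the apparent relative risk is 1.04, 1.06, 1.10 or 1.21. An observed difference of about 10 points is enough for significance.

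**The case against.** **The plan does not deny the bias.** A reader might infer from the Blinding section that the authors claim freedom from reporting bias. No section says so. The Auditing section discloses possible unmasking and plans to measure perceived allocation. This stands: the fault is one unqualified sentence that another section contradicts. But measuring perceived allocation at follow-up describes unblinding; it does not prevent it.

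**Blinding may have meant only that patients are not told their arm.** The Auditing wording supports that reading. Even so, not being told is not blinding when the allocated treatment is visible and the comparator is usual care.

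**The nurse route is an inference.** A reader might conclude that the counselling nurses collect the QLQ-C30. The document does not say so. Auditing does not specify which outcomes nurses assess, and they also rate the urgency of needs during calls. Follow-up describes written questionnaires filled out by patients, and nothing says that intervention nurses hand out, help with or see them. This objection stands, so nurse influence on the primary endpoint is possible, not shown. Form logistics are also detail that an article commonly leaves to the full protocol, so their absence is not itself a fault. They matter here only because Auditing affirmatively gives these nurses an assessment role.

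**The remedy leaves the main route open.** Rerouting forms does not stop patients from knowing what they received, and a trial of supportive counselling against usual care cannot easily avoid that. This also stands.

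**Conclusion.** The patient-blinding statement is untenable on the article's own account of the intervention, and the Blinding and Auditing sections contradict each other. That part is certain. It follows that the self-reported primary endpoint is exposed to reporting bias, chiefly through patients' awareness and possibly through nurse involvement in assessment.

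The size of the bias is not derivable from the document. Under the assumed 2 to 5 point lift and SD of 20 to 30, with no true effect, two-sided rejection would be about 8% to 48% against 5%. The upper end needs the most extreme pair of assumptions. These figures show that modest bias could matter; they do not estimate what will happen, and they do not show that a positive result would be spurious.

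The point should be corrected. It does not call for a different sample size, intervention or primary measure.

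**What to change.** 1. Delete the patient-blinding sentence, describe the trial as open-label for patients and staff, and bring the Blinding and Auditing sections into agreement. If anything is withheld from patients, say exactly what.
2. State in Auditing which outcomes, if any, the intervention nurses assess.
3. Specify that the 8-week and 8-month questionnaires are completed by the patient alone and returned directly to the coordinating centre or the independent randomisation institute, without handling or help from the intervention nurses. If the full protocol already provides for this, a sentence saying so is enough.
4. Keep the question on perceived allocation, and report it as a description of unblinding.
5. Acknowledge, when the result is interpreted, that bias from patients' own awareness remains.

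The cost is a change of wording and, where not already in place, a direct return route for forms. Postal return may need reminders. No additional assessor is needed.
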